### Exclusion criteria

Patients were excluded if they (1) were assigned emergency status at primary (or secondary) triage (for any clinical reason); (2) did not reside in an RACF or resided in respite care; (3) were attended by ambulance and transported to ED care outside of OPEN AOS model operational hours (i.e. before 08:00 or after 20:00 Monday to Sunday); (4) were referred to OPEN AOS by any referrer other than ambulance services; or (5) received care outside the designated study period (1 July 2022 to 30 June 2023). (6) Patients included in the intervention group, i.e. those seen by OPEN AOS will be excluded from the control group.

### Data collection and linkage

Patients living in RACFs are identified upon arrival to ED within EDIS^®^ and recorded as arriving by ambulance from a nursing home. Data extraction will occur retrospectively from state-based and MNHHS databases. An anonymous unique identifier (linkage ID) will be assigned to all cases by the Queensland Health Statistical Service Branch (SSB), enabling linkage of data from all sources (Table 1). These data provided to the researchers will not contain any key patient identifying features such as Unit Record Number (URN), name, address or Date of Birth (DOB). However, data such as age, postcode, and health facility will be included in the collection.

**Table 1 Tab1:** Data sources, date ranges and data descriptions for the OPEN AOS evaluation study

Data Source	Time Period	Data Description
RADAR Registry	1 Jul 2022 to 30 Jun 2023	OPEN AOS activity plus outcome data including: • outcomes of intervention • time stamps • clinician delegation Patient demographics for matching variables
Emergency Department Information System (EDIS^®^)	1 Jul 2022 to 28 Jul 2023	ED presentations of cohort members at one of the participating hospitals. • outcomes of intervention • time stamps Patient demographics and RACF address (presentation postcode and suburb) for matching variables
Metro North Health Funding and Data Insights	1 Jul 22 to 28 Jul 2023	Costs of initial ED presentations and subsequent re-presentations within 48 h and 28 days Patient unit record number for matching variables
Queensland Hospital Admitted Patient Data Collection	1 Jul 2020 to 30 Jun 2023	Patient co-morbidities identified during any hospital admission (using ICD-10-AM codes and ICD-10-AM code chapters), during the 24-month period preceding their presentations to the ED Patient demographics for matching variables
Death Registrations from the Registry of Births, Deaths and Marriages Queensland Cause of Death Unit Record File from the Australian Coordinating Registry	1 Jul 2022 to 02 Jul 2023	Death within 48 h of discharge from either emergency department presentation or OPEN AOS intervention Patient demographics for matching variables
RiskMan Queensland Health’s system for recording and managing clinical incidents, workplace events, consumer feedback, and risk	1 Jul 2022 to 02 Jul 2023	Patient Clinical Incident data within 48 h of discharge from the ED Patient demographics for matching variables
Queensland Ambulance Service Clinical & Dispatch Data (DARF and CAD)	1 Jul 2022 to 30 Jun 2023	Queensland Ambulance Service data including; • ambulance dispatch response variables • case cycle times (or time stamps) Patient demographics and clinical care variables for matching

*CAD* Computer Assisted Dispatch, *DARF* Digital Ambulance Report Form, *ED* Emergency Department, *ICD-10-AM* International Classification of Diseases, 10th Revision Australian Modification, *OPEN AOS* Older Persons Emergency Service Acute Outreach Service, *RADAR* Residential Aged Care District Assessment and Referral

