## Study design

This pragmatic multi-methods study comprises three discrete but related components: concurrent retrospective quantitative data collection for Components 1 and 2, and prospective qualitative data collection for Component 3. The approach to quantitative and qualitative data collection enables a comprehensive examination of the model’s effectiveness and real-world application. Given the multi-methods design, integration of quantitative and qualitative data through triangulation will not be undertaken. The design is underpinned by the integrated Practical, Robust, Implementation and Sustainability Model (PRISM) and Reach, Effectiveness, Adoption, Implementation and Maintenance (RE-AIM) framework [45]. PRISM will support the identification and description of contextual factors impacting RE-AIM outcomes [45]. This study has been reviewed and approved by the Metro North Human Research Ethics Committee (HREC) B (ECOO168), approval number 102,923. Data storage, retention and disposal will be conducted in accordance with the National Health and Medical Research Council (NHMRC) guidelines [46].

Three components are planned to address the following research questions:

*Component 1*

To what extent (if any) do patient characteristics (such as age, sex, and diagnostic classification^6^) and outcomes differ between OPEN AOS care and standard care (i.e. ambulance attendance with transport to ED care)?Specifically:

4.Primary Outcome: Time to be seen by treating clinician, defined as the amount of time in minutes from the initial contact with QAS to the time seen by either (i) the OPEN AOS clinician (intervention group) or (ii) the ED medical officer (control group).5.Secondary Outcomes:6.Length of care episode, defined as the amount of time in hours from initial contact with QAS to discharge of care.7.Ambulance transport to ED care: defined as the proportion of OPEN AOS patients requiring transport to ED for definitive care.8.ED re-presentation for any cause within 48 h and 28 days of discharge.9.Death within 48 h of discharge.10.Clinical incident^7^ [47] data, defined as clinical incidents that are reported by MNHHS staff that occur within 48 h of discharge.

*Component 2*

Compared to standard care, what is the incremental cost (saving) per person of the OPEN AOS model? 

*Component 3*

How do contextual factors influence implementation and potential future scale and spread of the OPEN AOS model?

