### Samples

In the 12-month study period from 1 July 2022 to 30 June 2023, approximately 7600 ED presentations from RACFs arrived by ambulance to district’s ED sites. During that same period, 735 patients were treated by OPEN AOS during their operational hours (08:00–20:00) Monday to Sunday. Patients treated in the Intervention group will be matched with up to three randomly selected control group patients without replacement with matching on age (+/- 5 years), and exact matching on sex and diagnostic classification section (or chapter if diagnoses are uncommon) as per the International Classification of Diseases, 10th Revision Australian Modification (ICD-10-AM) using the ‘R’ package Matching: Multivariate and Propensity Score Matching with Balance Optimization [50]. Groups sizes of 351 for the intervention group and 1053 for the control group will achieve 90% power to reject the null hypothesis of no effect on the time to be seen by treating clinician when there is a Cohen’s d small effect size of 0.2 using a two-sided, two-sample test assuming equal variance and an alpha of 5% [51].

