### Data analysis

For our analysis, the comparison of interest is between the intervention and control groups. Re-presentations by patients in either group are not considered as independent events and will be excluded from analyses, however the number of re-presentations during the study period will be noted for the OPEN AOS group. Categorical data will be presented as frequency and percentages, while continuous data will be reported as mean with standard deviation or median with interquartile ranges, depending on the distribution of the data. Categorical data will be analysed using the Pearson Chi-squared test or Fisher’s exact test, and continuous variables using the Student t-test or Mann-Whitney U test. Time to treating emergency clinician and time to discharge from the episode of care will be examined using a generalised linear model or parametric regression model if events are censored e.g., death of a patient. ED re-presentation and mortality will be examined using logistic regression if there are sufficient events. All regression models will be multivariable with fixed effects for triage score, weekend presentation, season, and ambulance referral time. The inclusion of Charlson Comorbidity Index [52] in regression analyses will depend on the extent of missing data. Component 1 will be reported in accordance with the Enhancing the QUAlity and Transparency Of health Research (EQUATOR) guidelines for reporting non-randomised studies [53].

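### The ED re-presentation comparison is not adjusted for prior hospital use, although admissions in the 24 months before each index episode are already in the requested data

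*Protocol article*

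**What the plan says.** The Study design section lists among the secondary outcomes "ED re-presentation for any cause within 48 h and 28 days of discharge". The Component 1 Data analysis section gives the model: "ED re-presentation and mortality will be examined using logistic regression if there are sufficient events". The covariates are stated for every model: "All regression models will be multivariable with fixed effects for triage score, weekend presentation, season, and ambulance referral time". One more is conditional: "The inclusion of Charlson Comorbidity Index [52] in regression analyses will depend on the extent of missing data". The Samples section matches on age, sex and ICD-10-AM diagnostic section or chapter. None of these is a measure of earlier hospital or ED use.

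Table 1 (Data collection and linkage) sets the extract dates. EDIS runs "1 Jul 2022 to 28 Jul 2023". The Queensland Hospital Admitted Patient Data Collection runs from 1 July 2020 to 30 June 2023, and its stated purpose is "Patient co-morbidities identified during any hospital admission" over the preceding 24 months.

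The Inclusion criteria take a control's earliest presentation in the study year as the index and allow an OPEN AOS patient more than one episode. The Exclusion criteria (item 6) remove anyone seen by OPEN AOS from the control pool. In Component 2, the costs of standard care take ED re-presentation from Component 1.

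**The concern.** A resident's own recent hospital use is a natural baseline measure of the tendency to return to hospital, which is what the re-presentation outcome records. In a non-randomised comparison, an imbalance in it that is neither matched nor modelled is read as an effect of the service.

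There are three reasons to expect that the groups may differ:

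- OPEN AOS clinicians decide which referrals suit the service, so allocation follows clinical judgement.
- Controls enter at their first presentation in the study year. The article does not say that an OPEN AOS episode must come before the resident's ED visits in that year.
- Residents who call often have more chances to reach OPEN AOS at least once, and are then removed from the control pool.

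The last two would tend to put frequent users in the OPEN AOS group. Clinical selection could add to this or offset it. A distorted re-presentation estimate would also pass into the incremental cost per patient.

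**Working it through.** **Scope check.** The plan's one computed figure is the sample size for the primary time outcome. With d = 0.2, 1:3 allocation, two-sided 5% and 90% power, n = (1 + 1/3) × (1.960 + 1.2816)² / 0.2² = 1.333 × 10.507 / 0.04 = 350.2, so 351 and 3 × 351 = 1053. This agrees with the plan, and nothing here changes it.

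**What each extract can show before the index episode.** Index episodes fall "In the 12-month study period from 1 July 2022 to 30 June 2023".

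| Index date | EDIS look-back (starts 1 Jul 2022) | Admitted-patient look-back (starts 1 Jul 2020) |
|---|---|---|
| 1 Jul 2022 | 0 days | 730 days, the full 24 months |
| 30 Jun 2023 | 364 days | the full 24 months (back to 30 Jun 2021) |

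EDIS therefore gives prior ED visits on no common basis. The admitted-patient extract gives prior admissions on a common 24-month basis for everyone. The Charlson index needs diagnosis codes, which is why missing data are a concern for it. A count of admissions does not, because zero is a valid value.

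**Where prior use could enter.** Matching: age, sex, diagnosis. Models: triage score, weekend, season, ambulance referral time, and the Charlson index if data allow. Prior use is in neither.

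**Illustration of size.** The inputs are assumptions, not figures from the documents: risk without prior use p0 = 10% or 15%; prior use multiplies risk by RR = 1.5, 2 or 2.5; prevalence f of prior use is 30% in one group and 40% or 50% in the other; no true effect.

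Group risk = p0 × (1 + f × (RR − 1)); the odds ratio (OPEN AOS over control) follows from the two group risks.

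- Smallest case, p0 = 0.10, RR = 1.5, f = 0.4 in OPEN AOS and 0.3 in controls: risks 0.120 and 0.115, odds ratio 1.05. With the prevalences exchanged: 0.95.
- Largest case, p0 = 0.15, RR = 2.5, f = 0.5 and 0.3: risks 0.2625 and 0.2175, odds ratio 1.28. Exchanged: 0.78.

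Across the grid the range is 1.05 to 1.28 if prior use is commoner in OPEN AOS, and 0.78 to 0.95 if it is commoner in controls. These are crude odds ratios. They take no account of the matching, the triage score or any Charlson adjustment, each of which may absorb part of the difference.

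**The case against.** The strongest case against is that this is a preference for one more covariate. Leaving out prior use contradicts nothing in the article. The article condenses a fuller protocol, and the Limitations section already concedes baseline differences and unmeasured confounding. Prior use correlates with morbidity, so diagnosis matching, triage score and the Charlson index may capture some of it. The imbalance is assumed, and its direction is unknown.

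Most of that stands, and it limits the point to a modest one. It does not remove it. The article states the covariates for all regression models, and a general caveat about unmeasured confounders does not cover one that can be counted from data already requested. The Charlson index is conditional and measures illness, not use.

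A second objection concerns a 12-month count of ED visits. For a control indexed late in the year, the first-presentation rule excludes earlier qualifying visits since 1 July 2022, so the count partly encodes group and index date. OPEN AOS care since January 2022 could also have lowered ED counts in one group only. Both are fair, and are why an admission count is the better choice. The first affects recent admissions too, hence the sensitivity version below.

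A reader might also infer from the EDIS start date that July 2022 index episodes following a June 2022 visit breach the plan's own exclusion: "Re-presentations by patients in either group are not considered as independent events and will be excluded from analyses". The documents do not support this. That sentence keeps one independent record per patient, and the control index is defined as the first presentation inside the study period. No washout before July 2022 is required, so none is missing.

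**Conclusion.** The point holds in a limited form. The re-presentation models omit prior hospital use, the groups are formed in ways that could make it differ, and a 24-month admission count is available for every index episode from data already requested. Any imbalance left after matching and adjustment would be read as an effect of OPEN AOS and carried into Component 2.

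The size and direction of any bias cannot be derived from the documents. The odds ratios above rest wholly on the assumed risks and prevalences.

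Some stronger readings should be resisted. ED re-presentation is a secondary outcome, and it is modelled only if events suffice; the primary outcome and its sample size are not affected. The EDIS dates are not in themselves an error: they cover the 28-day follow-up of the last index case. Nor does the point call for more terms in the 48-hour mortality model, where events may be few.

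**What to change.** 1. Add to the ED re-presentation models (48 hours and 28 days) the number of hospital admissions in the 24 months before the index QAS contact, derived in the same way in both groups, with zero as a valid value.
2. Report a sensitivity version that counts only admissions before 1 July 2022. Taking 1 July 2020 to 30 June 2022 for everyone gives the same 730 days per patient and keeps the control first-presentation rule from shaping the count. Admissions from January to June 2022 could still reflect early OPEN AOS care, which should be noted.
3. Use the adjusted re-presentation results when Component 1 feeds Component 2.

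The cost is one degree of freedom in each re-presentation model and no new data. Residents who moved from outside the area covered by the collection may show a false zero, which is a limitation to report. An earlier EDIS start date to obtain prior ED visits is optional; it would need a change to the data request, and the resulting count carries the weaknesses described above.

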## Control: standard ambulance model of care

In Queensland, prehospital emergency care is provided by the Queensland Ambulance Service (QAS), a single, state-wide, government-funded emergency ambulance service. Like other Australian and international ambulance services, primary triage of calls is completed by a non-clinical Emergency Medical Dispatcher to determine the nature and type of incident, and the response time criticality. All incidents are assigned as either: emergency (potentially life threatening – immediate response with lights and siren); urgent (acute – immediate response with no lights and siren); or non-emergency (time critical scheduled conveyance or routine) response. Incidents are subsequently assigned either an immediate dispatch response or are transferred for clinical review performed by a multidisciplinary team of experienced paramedics, medical practitioners, mental health clinicians, social workers and Registered Nurses (RNs). Following clinical review, patients are assigned the most appropriate health response, which may include a dispatch response or referral to equivalent care pathway, and/or virtual care (i.e., health care consultation provided via telehealth platform run by RNs and medical practitioners). The majority of QAS patients (over one million annually) are transported from the scene [38], and approximately 90.0% of transports are to public hospital EDs [39].

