### Inclusion criteria

Intervention: Adults aged 65 years or older who are permanent residents of RACFs situated within the MNHHS district geographical catchment area, with acute care needs and who were referred by the ambulance service to OPEN AOS between 08:00 and 20:00, Monday to Sunday, from 1 July 2022 to 30 June 2023. Patients can receive treatment by OPEN AOS on more than one occasion within the study period.

Control: Adults aged 65 years or older who are permanent residents of RACFs situated within the MNHHS district geographical catchment area, who received standard ambulance attendance and transport to a MNHHS ED between 08:00 and 20:00, Monday to Sunday, from 1 July 2022 to 30 June 2023. Only the first presentation for each patient within the study period will be examined.

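### Any-cause ED re-presentation is counted only at participating hospitals, and only controls are selected on using an MNHHS ED, so capture is incomplete and may differ between groups in favour of OPEN AOS

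*Protocol article*

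**What the plan says.** **Outcome.** Study design lists, among the Component 1 secondary outcomes, "ED re-presentation for any cause within" 48 hours and 28 days of discharge. It names no hospital or district.

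**Source.** In Data collection and linkage, the EDIS row of Table 1 covers "ED presentations of cohort members at one of the participating hospitals", from 1 July 2022 to 28 July 2023. The costs of index and repeat ED visits come from a Metro North source. The table lists no state-wide ED collection. Ambulance data are listed for dispatch variables, case times and matching, and end on 30 June 2023.

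**Eligibility.** Under Inclusion criteria, both groups are "permanent residents of RACFs situated within the MNHHS district geographical catchment area". Intervention patients are further described as those "with acute care needs and who were referred by the ambulance service to OPEN AOS between 08:00 and 20:00". Controls are those "who received standard ambulance attendance and transport to a MNHHS ED".

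**Analysis.** Samples matches on age, sex and diagnostic classification. The Component 1 Data analysis section plans logistic regression for re-presentation if events suffice. Its covariates are triage score, weekend, season and ambulance referral time, with the Charlson index if missing data allow. Component 2 takes re-presentation from Component 1 as an input to costs.

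**The concern.** The definition and the data source do not agree. The definition covers any ED; the source covers a subset. A re-presentation elsewhere is not set to missing. It enters the logistic regression as a non-event.

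Equal loss in both groups would lower both rates but leave their ratio unchanged. The eligibility rules give a reason to doubt that the loss is equal. Every control has, by selection, been taken at least once to the hospital system in which the outcome is later recorded. No intervention patient has to meet that condition. A catchment resident whose ambulance trips go to an ED outside MNHHS cannot become a control through such a trip, but can become an OPEN AOS patient. If hospital use is at all stable within a person or a facility, the missed share is larger in the intervention group.

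Neither the matching nor the covariates carry facility location or usual hospital, so nothing in the stated analysis would remove the difference. The error would favour OPEN AOS on one of its main safety outcomes. It would also pass into the Component 2 cost comparison for any missed visit to a public ED.

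**Working it through.** **The plan's own figure.** The article gives no planning figure for re-presentation. Its only sample size is for the primary outcome: d = 0.2, two-sided alpha 5%, power 90%, three controls per intervention patient. Recomputation gives 350.3 intervention patients, rounded up to 351, and 351 × 3 = 1053 controls, with power 90.1%. The stated 351 and 1053 are reproduced. They are used below only as group sizes.

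**Inputs.**
- True re-presentation rate p, the same in both groups (no true effect). Not in the article; assumed 10%, 20% or 30%.
- Missed share m: the proportion of re-presentations that occur outside the participating EDs, m_I for intervention and m_C for control. Not in the article; assumed.
- The nearest figure is in the section on the standard ambulance model: "approximately 90.0% of transports are to public hospital EDs". It describes all ambulance patients state-wide. It shows that trips to other destinations occur; it is not a rate of visits to other EDs by aged care residents.

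**Formula.** Observed rate = p × (1 − m) in each group. With the same p, observed RR = (1 − m_I)/(1 − m_C), whatever p is.

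**Results.** The last column is the chance of a significant result favouring OPEN AOS when there is no true effect, with 351 and 1053 patients, for p = 10%, 20% and 30%. The nominal value is 2.5%.

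| m_I | m_C | Observed RR | Observed rates if p = 20% | False result favouring OPEN AOS |
|---|---|---|---|---|
| 10% | 10% | 0.90/0.90 = 1.00 | 18.0% v 18.0% | 2.5%, 2.5%, 2.5% |
| 10% | 5% | 0.90/0.95 = 0.95 | 18.0% v 19.0% | 4.4%, 5.9%, 7.6% |
| 10% | 0% | 0.90/1.00 = 0.90 | 18.0% v 20.0% | 7.4%, 12.2%, 18.3% |

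**What the rows mean.** Suppose 10% of ED trips go elsewhere. If the destination is independent from trip to trip, a control's index trip says nothing about the next one. Both groups then lose 10%, and the first row applies. If instead 10% of residents always go elsewhere and re-present as often as the others, none of them can be a control, and the third row applies. Partial stability lies between.

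**Timing.** The last index date is 30 June 2023, and 28 days later is 28 July 2023. EDIS runs to that date. The ambulance extract does not, so as specified it could not be used to find late re-presentations at other EDs.

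**The case against.** The strongest reply is that nothing in the article shows that any resident uses an outside ED, or how often. Both groups live in one catchment served by five public hospitals, so the difference in missed shares may be close to zero. Controls' outside visits are missed as well. The state-wide 90% covers every kind of transport at all ages. All of this stands, and it limits the point to incomplete and possibly differential capture.

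A reader might go further and infer that OPEN AOS re-presentations are demonstrably under-counted, or that a relative risk near 0.8 should be expected. The documents do not support that. An RR of 0.84 needs, for example, 20% missed in the intervention group against 5% in controls, and no figure in the article points to such shares.

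Three further replies have partial force. First, Component 2 takes the perspective of the public hospital and health system, so private ED visits largely fall outside it; only missed visits to public EDs matter there. Second, the article does not name the participating hospitals, and it refers to Additional file 2 for outcome details, which is not shown. Reading them as the MNHHS EDs is an inference, though the article's own source list contains nothing wider. Third, the 30 June end of the ambulance extract is not an error in itself, because those data are not listed for this outcome.

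The Limitations section does name selection bias and unmeasured confounding. Incomplete outcome capture is a different problem, and it is not mentioned.

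**Conclusion.** The point holds in a limited form. As written, the plan measures re-presentation to participating EDs and calls it any-cause ED re-presentation. Its eligibility rules make loss of events plausibly greater in the OPEN AOS group. The likely direction favours OPEN AOS, on this secondary safety outcome and, for public EDs outside the participating sites, in the Component 2 costs.

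The size cannot be derived from the documents. The illustrations run from no bias in the ratio (equal shares) to an RR of 0.90 (10% against none). They rest on assumed missed shares and on no true difference between groups. The primary outcome, time to be seen, and its sample size are not affected. It is worth correcting because the remedy is cheap and the outcome carries much of the safety claim.

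**What to change.** 1. Ask the state linkage unit for public ED presentations state-wide, to 28 July 2023, for both groups, and count the outcome from these.
2. Add transport destination to the ambulance data and extend that extract from 30 June to 28 July 2023, so that ambulance re-presentations at any other ED, private ones included, can be identified. Visits to those EDs by other means would still be missed; say so.
3. If neither can be obtained, restate the outcome as re-presentation to participating EDs, and list those hospitals. Add a sensitivity analysis restricted, in both groups, to facilities (or facility postcodes) whose ambulance transports go almost wholly to those EDs. Carry the same restriction into the Component 2 re-presentation input.
4. Add incomplete and possibly differential outcome capture to the limitations.

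The cost is a wider data request, four more weeks of ambulance data and somewhat more linkage work. The linkage unit is already engaged and already links state-level admission and death data, and no patient needs to be contacted. The restricted sensitivity analysis would lose some patients and precision.

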However, the coordination and continuity of care for the older adult remains paramount [28, 29]. There are key considerations when providing acute care to an individual in the RACF such as: ascertaining their goals of care; treatment beneficence; non-maleficence (e.g. avoiding futile treatment); and understanding the capacity to diagnose and manage care safely in the home [30]. Various medical problems can be effectively treated and managed in the resident’s home such as urinary tract infections and falls with minor injuries including skin tears or simple lacerations [31]. A recent systematic review of ED transfers determined up to 55% were potentially avoidable, meaning the resident was safe to remain in their home utilising alternative care pathways [32]. Additionally, some evidence suggests that RACF residents and their families have a general preference for treatment to be provided in their home environment [33].

A systematic review of 15 observational studies evaluating acute outreach models of care to people living in RACFs on ED transfer prevention, hospitalisation, safety, cost-effectiveness and experiences [34] highlighted the absence of evidence. The authors recommended that future cluster-randomised or quasi-experimental studies be undertaken to assess the effectiveness and safety of these new outreach models [34].

To support the provision of emergency care for residents in RACFs in Queensland Australia, a novel acute ED substitution outreach model called OPEN AOS (Older Persons Emergency Network Acute Outreach Service) was established. The overarching aim of this study is to evaluate the implementation and outcomes of this ED outreach model. This paper describes the protocol for the evaluation of the OPEN AOS model.

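### Death is counted only to 48 h while ED re-presentation runs to 28 days, so a death on days 3-28 before any return to ED is a non-event on both outcomes

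*Protocol article*

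**What the plan says.** Aim 1 (Study aims) is to compare effectiveness and safety with standard care. The Component 1 secondary outcomes (Study design) use different follow-up lengths:

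- Re-presentation: "ED re-presentation for any cause within 48 h and 28 days of discharge".
- Mortality: "Death within 48 h of discharge".
- Clinical incidents: "clinical incidents that are reported by MNHHS staff that occur within 48 h of discharge".

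Table 1 (Data collection and linkage) matches these windows. The EDIS extract runs "1 Jul 2022 to 28 Jul 2023". The death sources run "1 Jul 2022 to 02 Jul 2023" and are described as supplying "Death within 48 h of discharge from either emergency department presentation or OPEN AOS intervention".

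On analysis, the Component 1 Data analysis section states that "ED re-presentation and mortality will be examined using logistic regression if there are sufficient events". It mentions death as a censoring event only for the two time outcomes, time to clinician and time to discharge. It does not say how a death affects the 28-day re-presentation outcome.

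**The concern.** In frail residents of aged care facilities, death competes with a return to ED. Someone who stays in the facility and dies there on day 5 has not re-presented, which is the favourable result on that outcome, and is not a death under the 48 h definition. No other listed outcome counts the event, because clinical incidents also stop at 48 h.

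Two things are at stake. First, the safety comparison has no mortality result beyond 48 h, although the plan treats 28 days as a relevant period for any-cause re-presentation. Second, a low 28-day re-presentation rate is ambiguous, because it may reflect recovery at home or death at home.

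Equal mortality in the two groups cannot be presumed. Allocation is not random, OPEN AOS clinicians triage each referral for suitability, matching is on age, sex and diagnosis only, and adjustment for the Charlson index depends on how much is missing.

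**Working it through.** **The plan's own figure.** The only sample-size statement concerns the primary outcome. With d = 0.2, two-sided alpha 5%, 90% power and a 1:3 ratio, n = (1.960 + 1.282)² × (1 + 1/3) / 0.2² = 350.2, so 351 and 3 × 351 = 1053. Power at those sizes is 0.900. The figure reproduces and is not affected by this point.

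**Dates.** The last study day is 30 June 2023.

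- Death extracts end 2 July, which is 2 days later. EDIS ends 28 July, which is 28 days later. The gap is 26 days.
- The last discharge date with 28 full days inside the death extract is 2 July minus 28 days = 4 June 2023. From 1 July 2022 to 4 June 2023 is 339 of 365 days, or 93%.

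For most of the year, then, the extract dates already span 28 days. What leaves later deaths out is mainly the 48 h outcome definition and the 48 h data description. The dates themselves cut the window only for discharges after 4 June.

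**Who is affected.** Only residents who die on days 3-28 before any re-presentation. Those who return to ED first and die later are counted correctly as re-presenting.

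**Effect on the re-presentation comparison.** The article gives no event rates, so all of these are assumptions: 20% would re-present within 28 days in both groups if nobody died, and 28-day mortality is 15% in one group and 5% in the other.

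- *Constant hazards.* h = −ln(1 − risk)/28, and observed re-presentation = h_r/(h_r + h_d) × [1 − exp(−28(h_r + h_d))]. With h_r = 0.00797 and h_d = 0.00580 or 0.00183, this gives 18.5% at 15% mortality and 19.5% at 5%, a difference of 1.0 point.
- *All deaths at day 4.* The chance of re-presenting before day 4 is 1 − 0.80^(4/28) = 0.0314. Observed: 0.85 × 0.20 + 0.15 × 0.0314 = 17.5%, and 0.95 × 0.20 + 0.05 × 0.0314 = 19.2%, a difference of 1.7 points.
- *Range.* With underlying re-presentation of 10% to 30%, the same two models give 0.5 to 2.5 points. With mortality of 6% versus 3% and 20% re-presentation, they give 0.3 to 0.5 points. With equal mortality the difference is zero.
- *Direction.* Whichever group has the higher mortality looks better on re-presentation. Swapping the two mortality figures reverses the sign.

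For scale, the 95% half-width for a difference of 18.5% versus 19.5% at 351/1053 is 1.96 × √(0.185 × 0.815/351 + 0.195 × 0.805/1053) = 4.7 points. The distortion is well inside sampling error.

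**What goes unreported.** Under the same 15% versus 5% with constant hazards, 48 h mortality is 1 − 0.85^(2/28) = 1.2% versus 1 − 0.95^(2/28) = 0.4%. The 48 h outcome shows about 0.8 of the 10-point gap, and none of it if the deaths fall at day 4. The composite of re-presentation or death by day 28 is 1 − 0.80 × 0.85 = 32% versus 1 − 0.80 × 0.95 = 24%, a visible difference of 8 points.

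**Precision.** With equal risk p in both groups, the 95% interval for the risk ratio is the estimate multiplied or divided by exp{1.96 √(1/a − 1/n₁ + 1/b − 1/n₂)}, where a and b are the expected deaths.

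| Assumed p | Group sizes | Expected deaths | Factor |
|---|---|---|---|
| 1% (48 h) | 351 / 1053 | 3.5 / 10.5 | 3.3 |
| 8% (28 days) | 351 / 1053 | 28 / 84 | 1.5 |
| 1% (48 h) | 735 / 2205 | 7.4 / 22 | 2.3 |

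The last row uses all 735 treated patients with three controls each, an upper limit because not all need be eligible.

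**The case against.** The 48 h window is a coherent choice: deaths, clinical incidents and early re-presentation all use it, and a death close to discharge is easier to attribute to the episode. Later deaths in frail residents depend more on prior health, which matching on age, sex and diagnosis does not fully balance. That stands as a caution about interpretation. It is not a reason to leave the deaths unreported, since 28-day re-presentation is open to the same confounding and is already an outcome.

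Competing-event methods are commonly left to an analysis plan. That is fair, but such a plan could apply them only with deaths to day 28, and the protocol fixes the death outcome and data item at 48 h.

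A reader might infer several stronger claims that the document does not support:

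- *That the plan favours OPEN AOS.* Selecting suitable cases could mean lower mortality in that group, which would reverse the bias. The article's remarks on goals of care and futile treatment are general background on acute care in facilities, not a stated OPEN AOS selection rule.
- *That the data cannot show these deaths.* The extract dates span 28 days for discharges on 93% of study days.
- *That the Component 2 cost model is biased.* A resident who has died incurs no later ED cost, so the observed re-presentation probability is the right input for expected cost per patient.
- *That the plan concedes 48 h deaths will be too few.* The condition about sufficient events covers re-presentation as well and is routine.

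**Conclusion.** The point holds in a limited form and is a cheap improvement. As fixed in the protocol article, a death on days 3-28 before any return to ED is a non-event on both the mortality and the re-presentation outcome. The safety comparison therefore says nothing about such deaths, and 28-day re-presentation cannot be read on its own as a sign of good care.

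The main loss is the unreported mortality comparison. The re-presentation comparison is distorted only if day 3-28 mortality differs between these non-randomised groups. The distortion is then modest, about 1 to 2 points at 15% versus 5%, and could run either way. These sizes rest entirely on assumed rates. The mismatch between the windows is read directly from the text and does not depend on them.

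**What to change.** 1. In Table 1, extend both death sources from 2 July to 28 July 2023, matching EDIS, and widen the data description from 48 h to 28 days.
2. Add death within 28 days of discharge as a secondary safety outcome in both groups, keeping the 48 h outcome.
3. Report 28-day re-presentation alongside the composite of ED re-presentation or death within 28 days, or with death as a competing event. Draw no favourable conclusion from re-presentation alone.

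The cost is 26 more days on an extract that is already being linked, one added outcome and one added model, with perhaps a minor ethics or data-custodian variation. No new patients are needed and the sample size does not change. The price in interpretation is that 28-day death is more open to confounding than 48 h death, so it should be read with the caveats on non-randomised comparison already given under Limitations.
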